#### 3.5.2.4 Vital Signs

Respiration rate, pulse rate and sitting blood pressure after 5 minutes of rest.

#### 3.5.2.5 Physical examination

Information about the physical examination must be present in the source documentation at the study site. Significant findings that are present prior to the start of the study drug must be included in the Relevant Medical History case report form or Current Medical Conditions case report form. Significant findings made after the start of the study drug which meet the definition of an AE must be recorded in the Adverse Event case report form.

The examination of the following will be performed: eyes, ears, nose and throat; heart; peripheral vasculature; lungs; musculoskeletal system, abdomen, neurologic function (with testing for diabetic sensory neuropathy), endocrine system, skin and lymph nodes.

#### 3.5.2.6 Body Fat Mass

Body fat mass will be estimated from measurements with Lange skin-fold calipers at biceps, triceps, subscapular, and iliac crest sites.

#### 3.5.2.7 Skin Thickness

Skin thickness will be measured at four sites ( the right and left hand and the right and left volar forearm) using Harpenden calipers.

#### 3.5.2.8 Body Weight

Subjects will be weighed clothed without shoes.

#### 3.5.2.9 Waist/Hip Measurements

Waist will be measured at the smallest abdominal circumference while hips will be measured at the largest gluteal circumference using a tape measure.

### 3.5.3 Drug Concentration and Pharmacokinetic Evaluations

Not applicable.

## 4. Statistical Methods

### 4.1 Statistical Methods to be Employed

#### 4.1.1 Study Objectives

This is a Phase II, placebo-controlled, comparative study. The primary objective is to evaluate the safety of two doses (1 mg and 2 mg by daily subcutaneous injection) of TH9507 relative to placebo administration, over a 12-week period in patients with stable, type 2 diabetes.

The primary endpoint is the change in relative insulin response following the oral ingestion of glucose over the 12-week treatment period. The relative insulin response is defined as the ratio of the incremental plasma insulin response above basal at 30 minutes to that of plasma glucose, divided by basal plasma insulin levels.

The secondary objectives are to evaluate the effects of 12 weeks of daily treatment with TH9507 on HbA1c, blood glucose measurements, **use of oral hypoglycemic agents and/or insulin and control of diabetes.**

The secondary endpoints include the change in HbA1c at Week 12 compared to baseline and changes in mean daily serum glucose concentrations compared to the 14 day lead-in period values, **changes in the number of dose adjustments per week for insulin and/or oral hypoglycemic agents compared to the 14 day lead-in period, and the number of subjects with a change in the control of diabetes.**

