## 1. Introduction

The somatotrophic axis regulates many essential physiologic functions. Although growth hormone (GH) was originally recognized for its primary role in effecting growth in stature, its importance in preserving anabolism and its involvement in tissue repair during adulthood have recently been more fully documented. The aging process, however, is associated with a blunting of basal and stimulated GH secretion. This early and progressive decrease in spontaneous GH secretion is associated with a decrease in blood levels of insulin-like growth factor 1 (IGF-1), the principal effector and marker of GH anabolic actions.

Experimental attempts to restore complete functionality of the somatotrophic axis in aged patients have included the administration of exogenous recombinant human growth hormone (rhGH) and analogues of growth hormone releasing factor (GRF). Administration of rhGH to these patients, however, has been associated with a variety of adverse effects including hyperglycemia, insulin resistance, fluid retention, carpal tunnel syndrome, and gynecomastia. These adverse effects have been shown to be more frequent in patients with the highest IGF-1 levels. Importantly, the IGF-1 negative feedback on GH secretion is inoperative during treatment with exogenous rhGH, and exogenous rhGH is unable to mimic the physiologic, pulsatile rate of endogenous GH secretion. While GRF is able to preserve the physiologic pulsatile pattern of GH secretion, rapid hydrolysis of natural GRF by dipeptidyl-amino peptidase in serum limits its efficacy as a treatment modality. Administration of a GRF analogue has been associated with enhanced insulin sensitivity in males, in contrast to the insulin resistance observed with the administration of rhGH.

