## 1.1 Rationale

The clinical development program for TH9507 includes its use in patients who could benefit from enhancement of anabolic effects, including patients with COPD, hip fractures, and other age-related disorders associated with somatopause. As noted, different changes in insulin sensitivity have been observed with rhGH and GRF analogue administration. It is anticipated that a number of patients to be enrolled in future trials of TH9507 will have glucose intolerance and/or overt diabetes. Therefore, the purpose of this study is to investigate the safety of daily administration of TH9507 in patients with type 2 diabetes mellitus, in particular, the potential for effects on insulin sensitivity and diabetic control.

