### 3.5.2 Safety Assessments

This is a study to assess the safety of 12 weeks of daily administration of TH9507. Safety assessments will include the monitoring and recording of all adverse events and any serious adverse events; the sequential assessment of hematology, blood chemistry, and urinalysis parameters; the monthly monitoring of HbA1c, periodic assessments of lipid profiles, including HDL, LDL, total cholesterol, and triglycerides; monitoring for antibodies to TH9507 before and after 12 weeks of treatment; and periodic measurements of blood pressure, as well as performance of physical examinations including screening testing for diabetic sensory neuropathy. This study will seek to assess any clinically meaningful changes in insulin sensitivity through use of sequential periodic oral glucose tolerance tests with paired insulin and glucose levels to determine insulin:glucose ratios.

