#### 3.5.2.3.6 Oral Glucose Tolerance Test (OGTT) with paired glucose and insulin levels

Blood glucose and insulin will be measured at 0 minutes (prior to ingestion of glucose), 30 minutes, 1, 1.5, 2, 2.5, and 3 hours. For these determinations, oral sulfonylureas, insulin, and other insulin secretagogues must be withheld on the morning of the OGTT. Insulin sensitizers need not be withheld at such times.

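### The primary endpoint cannot show insulin resistance that is matched by a proportional rise in insulin, and Section 4.1.1 names no insulin-sensitivity endpoint beside it

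*Protocol*

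**What the plan says.** Section 1.1 gives the purpose as safety in type 2 diabetes, "in particular, the potential for effects on insulin sensitivity and diabetic control". The background in Section 1 is that a GRF analogue was linked to better insulin sensitivity in males, "in contrast to the insulin resistance observed with the administration of rhGH".

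Section 3.5.2 takes this up as an assessment: "This study will seek to assess any clinically meaningful changes in insulin sensitivity through use of sequential periodic oral glucose tolerance tests". The same sentence says how, namely by "oral glucose tolerance tests with paired insulin and glucose levels to determine insulin:glucose ratios". It does not say which time points enter the ratios, and it mentions no division by basal insulin.

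Section 4.1.1 sets the primary endpoint as the change in relative insulin response. Its definition reads: "the ratio of the incremental plasma insulin response above basal at 30 minutes to that of plasma glucose, divided by basal plasma insulin levels". The hypotheses in Section 4.1.4 and the sample size in Section 4.1.5 rest on this index.

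The sentence in Section 4.1.1 that begins "The secondary endpoints include the change in HbA" goes on to list HbA1c, mean daily glucose, the weekly number of adjustments to insulin or oral agents, and the number of subjects whose diabetes control changes. No fasting-insulin or insulin-sensitivity measure, and no undivided insulin:glucose ratio, is on that list.

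The raw data are there. Section 3.5.2.3.6 schedules seven paired glucose and insulin samples per OGTT, one before the glucose drink and then one every half hour up to 3 hours.

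**The concern.** The index measures how far insulin rises in the first 30 minutes per unit of glucose rise, relative to where insulin started. That describes early secretion. A patient who becomes more resistant and compensates by running higher insulin throughout can have the same index as before.

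The two-sided hypothesis in Section 4.1.4 does not say how a movement in either direction would be interpreted. A reader of the final report could take an unchanged primary endpoint as evidence that insulin sensitivity was preserved, which the index cannot show. A fall could equally be reported as a secretion effect when it reflects resistance.

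Among insulin users the measured values may also include injected insulin. Section 3.5.2.3.6 requires only that "insulin, and other insulin secretagogues must be withheld on the morning of the OGTT", and Section 3.4.4 leaves dose changes during the trial to the investigators. The protocol does not say whether the assay detects injected insulin, so this is a possibility rather than an established bias.

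**Working it through.** **Inputs from the protocol.** Endpoint definition: Section 4.1.1. Baseline index 0.23 in the placebo group and Type I error 0.05: Section 4.1.5. Two-sided test: Section 4.1.4.

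**Assumed for illustration.** Basal insulin I0 = 15, fasting glucose G0 = 8, glucose increment G30 − G0 = 3.33. The protocol gives no such values and no units for the index. The cancellation in step 2 does not depend on them.

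**Step 1: match the protocol's baseline.** Index = [(I30 − I0)/(G30 − G0)]/I0. For an index of 0.23, I30 = 15 × (1 + 0.23 × 3.33) = 26.49. The undivided ratio is (26.49 − 15)/3.33 = 3.45, and 3.45/15 = 0.23.

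**Step 2: multiply all insulin values by a factor c, with the glucose increment unchanged.** Index = [c(I30 − I0)/(G30 − G0)]/(c × I0). The factor c cancels. For c = 1.15, 1.25, 1.5 and 2.0 the index stays at 0.23, while the undivided ratio rises by 15%, 25%, 50% and 100%. The true shift in the primary endpoint is zero, so the chance of rejection is the Type I error, 0.05, whatever the sample size.

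**Step 3: other patterns, fasting glucose held at 8.**

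| Pattern | I0 | Insulin increment | Glucose increment | Undivided ratio | Index | I0 × G0 |
|---|---|---|---|---|---|---|
| Start | 15 | 11.49 | 3.33 | 3.45 | 0.230 | 120 |
| All insulin × 1.5 | 22.5 | 17.23 | 3.33 | 5.18 | 0.230 | 180 |
| All insulin × 2 | 30 | 22.98 | 3.33 | 6.90 | 0.230 | 240 |
| Basal insulin + 50%, same increment | 22.5 | 11.49 | 3.33 | 3.45 | 0.153 | 180 |
| All insulin × 1.5, glucose increment + 15% | 22.5 | 17.23 | 3.83 | 4.50 | 0.200 | 180 |
| Insulin increment divided by 1.15 | 15 | 9.99 | 3.33 | 3.00 | 0.200 | 120 |

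The last two rows are the important ones. Partly compensated resistance and a plain loss of early secretion give the same index, 0.200. Fasting insulin times fasting glucose separates them (+50% against no change), and so does the undivided ratio (4.50/3.45 = +30% against 3.00/3.45 = −13%).

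**Step 4: do the named secondary endpoints fill the gap?** HbA1c and home glucose measure glycaemia. Background treatment may be adjusted during the trial (Section 3.4.4), which can offset a change in either. The adjustment endpoint counts changes per week and carries neither direction nor size. The control-of-diabetes endpoint is a count of subjects. Each can respond to a change in sensitivity, but none measures it.

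**The case against.** The algebra is not in dispute. The objections concern how far it reaches, and most of them limit the point.

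- A reader might infer that the trial as a whole would miss insulin resistance, or that its question would go unanswered. The protocol does not support that. Section 3.5.2 commits to insulin:glucose ratios from serial OGTTs expressly for sensitivity, and an undivided ratio does rise in the scenarios where the primary endpoint is flat. Resistance that is not compensated could show in HbA1c, home glucose or dose adjustments.
- A reader might infer that no endpoint could touch sensitivity. That is too absolute. The list in Section 4.1.1 is open-ended. Section 4.1.9 treats changes in biochemical laboratory parameters as secondary endpoints, and Section 3.5.2.3 lists insulin and glucose among the assays. Fasting insulin is not named there, so its status is arguable. A SAP may also derive further indices.
- The blindness is complete only when basal and 30-minute insulin rise by the same factor and the glucose increment does not change. The protocol gives no reason to expect exactly that pattern. Other patterns move the index, though ambiguously.
- The primary objective is safety in general, and no direction of effect is specified.
- Injected insulin is partly addressed by stratified randomization (Section 4.1.6) and adjustment for insulin use (Section 4.1.4). Dose changes after randomization would affect a fasting-insulin or OGTT sensitivity index too.

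What stands is that the protocol itself fixes the primary endpoint, hypothesis and sample size on a secretion index. It names sensitivity as a question in two places and does not carry the measure promised in Section 3.5.2 into the endpoints of Section 4.1.1.

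**Conclusion.** The concern holds in a limited form. For compensated resistance with an unchanged glucose increment, the primary endpoint has an expected shift of exactly zero and a rejection probability of 0.05 at any sample size. This rests on the definition alone. For other patterns the index moves but cannot distinguish greater resistance from weaker secretion; the figures 0.153 and 0.200 illustrate this with assumed insulin and glucose values and say nothing about how likely each pattern is.

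Sections 3.5.2 and 4.1.1 therefore do not match. The first promises an assessment of sensitivity; the second names no endpoint that delivers it. The defect lies in the endpoint list and in how an unchanged result might be read, not in the data collection. It should be corrected, but it does not invalidate the primary endpoint as a measure of early secretion. The conclusion does not depend on the sample-size calculation in Section 4.1.5.

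**What to change.** Reconcile Sections 3.5.2 and 4.1.1:

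1. Name one insulin-sensitivity measure from samples already drawn as the first-ranked secondary endpoint, for example fasting insulin times fasting glucose, or a composite index from the seven paired OGTT samples. Choose it before unblinding, and define the insulin:glucose ratios of Section 3.5.2 accordingly.
2. Analyse it with the repeated-measures model of Section 4.1.4, adjusted for insulin use.
3. Show it descriptively by insulin-use stratum, because injected insulin may enter the measured values. Under the cap in Section 4.1.6 the smaller stratum could be about 12 subjects, or 12/3 = 4 per arm, too few for separate inference.
4. State that an unchanged primary endpoint will not be read as unchanged insulin sensitivity, and keep the relative insulin response as the measure of early secretion.

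The cost is a small change of protocol wording, one derived variable, and one more secondary test under Section 4.1.13, which applies no multiplicity correction. A co-primary endpoint is not needed; it would require a multiplicity rule and changes to Sections 4.1.4 and 4.1.5. No new visits, sampling or C-peptide assay are needed.

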### 3.3.3 Interruption or Discontinuation of Treatment

Before interrupting or discontinuing study drug, the investigator must contact the sponsor or designee (except in the case of an emergency) to discuss the proposed reason. It will be documented whether or not each subject completed the clinical study. If any subject's study treatment or observations were discontinued, the reason will be recorded. Reasons that a subject may discontinue participation in this clinical study may be one or more of the following:

- Adverse event(s)
- Abnormal laboratory value(s)
  - Hemoglobin: decrease below 9.0 gm/dL
  - AST:  $\geq 3 \times$  ULN (upper limit of normal)
  - ALT:  $\geq 3 \times$  ULN
  - LDH:  $\geq 3 \times$  ULN
  - Alkaline Phosphatase:  $\geq 2 \times$  ULN
  - Triglyceride:  $\geq 1000$  mg/L
  - Creatinine:  $>2$  mg/dL
- **Any fasting glucose  $>300$  mg/dL and/or any HbA1c value of  $>12\%$  in spite of ad lib adjustments to oral hypoglycemic agents and/or insulin dosage.**
- Subject withdrew consent
- Lack of compliance to protocol requirements and/or procedures
- Lost to follow-up

- Administrative deviations which preclude satisfactory completion of protocol assessments

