#### 3.4.4 Concomitant Therapy

Oral or parenteral glucocorticoids will not be permitted during the study. Hormone replacement therapy for female subjects will be allowed. All other concomitant drugs should be maintained at constant dose during the study, if possible. Concomitant drugs will be recorded in the Case Report Forms.

Dose adjustments for insulin and/or oral hypoglycemics during the conduct of the trial will be at the discretion of the investigators.

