- Instruct the subject to withhold oral sulfonylurea, insulin, and other insulin secretagogues but he/she may take oral non-sulfonylurea hypoglycemic medication (if oral insulin sensitizer) in the morning of Visit 6 and Visit 7.
- Instruct the subject to collect urine the day before the scheduled visit (starting at 6AM) until the morning (6AM) of the clinic visit.
- Schedule Visit 6 to occur 25-31 days following Visit 5, OR
- Schedule Visit 7 to occur 25-31 days following Visit 6.

VISIT 7: (Week 12  $\pm$  3 days)

- Assess adverse events.
- Review concomitant medications.

- Return all used and unused study drugs.
- Obtain body weight.
- Obtain vital signs (BP, RR, PR).
- Determine body mass index.
- Perform funduscopy with dilation by optometrist or ophthalmologist (may be performed within 5 days of date of Visit 7).
- Perform physical/neurological examinations (including examination for diabetic sensory neuropathy).
- Review/dispense diary.
- Download home glucose readings from previous 4 weeks.
- Dietician interview and assessment – caloric intake assessment, skin thickness (Harpender), waist/hip measurements, and body fat mass (Lange).
- Collect 24-hour urine for creatinine and nitrogen.
- Obtain blood (fasting) for laboratory tests – IGF-1, IGFBP-1, IGFBP-3, serum for TH9507 antibody, lipid profile, hematology, chemistry, HbA1C.
- Perform oral 3-hr GTT with 75Gm Glucose (Glucola).
- Obtain blood for insulin and glucose levels every 30 minutes during OGTT
- **Remind the subjects to call the clinic for any home blood glucose value that is >250 mg/dL.**
- **Investigator completes global assessment of diabetes control**
- Replenish boxes of strips and lancets, if necessary
- Subject receives NO STUDY DRUG AT THIS VISIT.
- Schedule Visit 8 (Post-treatment Visit) to occur 25-31 days following Visit 7.

VISIT 8: (Week 16 ± 3 days; Follow-up Visit; 16 weeks after randomization; 4 weeks post-treatment)

- Assess adverse events.
- Review concomitant medications
- Obtain body weight.
- Obtain vital signs (BP, RR, PR).
- Obtain blood for laboratory tests (hematology; blood chemistry; lipid profile)
- Collect urine for urinalysis.
- Schedule mammography (for females) and prostate examination/PSA (for males).
- Dietician interview and assessment – caloric intake assessment, skin thickness (Harpender) , body fat mass (Lange), and waist/hip measurements.
- Review diary.
- Download home glucose readings for the period since Visit 7.

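### Two secondary endpoints, antidiabetic dose adjustments and diabetes control, are defined without direction, so they cannot by themselves separate worsening from improvement

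*Protocol*

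**What the plan says.** Section 4.1.1 of the protocol names four secondary endpoints:

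- HbA1c: "The secondary endpoints include the change in HbA 1c at Week 12 compared to baseline".
- Home glucose: "changes in mean daily serum glucose concentrations compared to the 14 day lead-in period values".
- Treatment: "changes in the number of dose adjustments per week for insulin and/or oral hypoglycemic agents compared to the 14 day lead-in period".
- Control: "the number of subjects with a change in the control of diabetes".

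The listed source for the last is in section 3.5.1 at Visit 7: "Investigator completes global assessment of diabetes control". No scale is given there. The diary dispensed at Visit 2 records adjustments to oral agents and insulin.

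On treatment during the trial, section 3.4.4 says "Dose adjustments for insulin and/or oral hypoglycemics during the conduct of the trial will be at the discretion of the investigators". Section 3.3.3 makes high glucose or HbA1c a possible reason for discontinuation only when it occurs "in spite of ad lib adjustments to oral hypoglycemic agents and/or insulin dosage".

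On the expected direction, section 1 describes insulin resistance with recombinant growth hormone, but also says "Administration of a GRF analogue has been associated with enhanced insulin sensitivity in males". Section 4.1.4 makes the primary analysis two-sided because no direction is specified.

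**The concern.** The study exists to find out whether the drug disturbs insulin sensitivity and diabetic control (section 1.1). When investigators may adjust treatment freely, one natural sign of harm is that patients need more treatment while HbA1c and glucose move little. A sign of benefit is that they need less.

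The adjustment endpoint is signed only as a frequency, that is, more or fewer adjustments than in the lead-in. Each adjustment is itself undirected: repeated increases and repeated decreases score alike. A count of subjects with a change in control has the same weakness if better and worse are added together. A difference between arms on either endpoint could then mean harm or benefit, and no difference could conceal opposite movements.

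**Working it through.** **1. The adjustment count.** Let U and D be upward and downward adjustments per week, with subscript 1 for treatment and 0 for lead-in. As worded, the endpoint is

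E = (U1 + D1) − (U0 + D0).

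Patients must have been on a stable regimen for at least 2 months before screening (section 3.3.2), so assume U0 = D0 = 0. Take one arm with U1 = 1, D1 = 0 and another with U1 = 0, D1 = 1. Then E = 1 in both. Counted separately, the changes from lead-in are (up 1, down 0) and (up 0, down 1), which are opposite results. This is a constructed extreme. It shows what the definition allows, not what is expected.

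**2. The control endpoint.** If both directions are pooled, the share with any change is the share worse plus the share better. The table gives exact two-sided Fisher power at alpha 0.05 with 13 per arm, the planned number of completers. The rates are assumptions; the documents give none.

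| Active worse / better | Placebo worse / better | Any change, active vs placebo | Power, any change | Power, worse |
|---|---|---|---|---|
| 60% / 10% | 10% / 10% | 70% vs 20% | 69% | 71% |
| 60% / 10% | 10% / 30% | 70% vs 40% | 26% | 71% |
| 60% / 10% | 10% / 60% | 70% vs 70% | 2% | 71% |
| 50% / 10% | 10% / 50% | 60% vs 60% | 3% | 49% |

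Pooling costs almost nothing if few placebo patients improve, and nearly all the power if many do.

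**3. How far HbA1c can be blunted.** First the plan's own figure: section 4.1.5 says 13 per group suffice for 80% power with a paired t-test, effect size 1 and alpha 0.05. With noncentrality 1 × √13 = 3.61 on 12 degrees of freedom, two-sided power is 91%, so that statement is true. Now assume that added medication offsets a share c of a true rise of 1 SD. The noncentrality becomes (1 − c) × 3.61:

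- c = 0: power 91%
- c = 25%: 70%
- c = 50%: 38%
- c = 75%: 13%
- c = 100%: 5%, the alpha level

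The offset share is not known. Sections 4.1.4 and 4.1.9 describe no allowance for medication change in the HbA1c or glucose analyses.

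**The case against.** The strongest reply is that other data carry direction.

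- Section 3.5.2.1 makes an abnormal result an adverse event when it requires therapeutic intervention, recorded under a diagnostic description. Section 4.1.9 rests the safety assessment mainly on adverse events and out-of-range laboratory values.
- The glucose tolerance tests are done with insulin and secretagogues withheld that morning (section 3.5.2.3.6), which partly limits masking.
- Concomitant drugs are recorded, hypoglycemic episodes go in the diary, home values above 250 mg/dL prompt a call, and section 3.3.3 catches extremes.

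This stands. A reader might infer that the two endpoints are the only ones that could reveal harm; the documents do not support that.

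A reader might also infer that the count grossly overweights trivial corrections: one lasting increase in 12 weeks scores 1/12 = 0.083 per week, while daily corrections score 7. That ignores the subtraction of the lead-in. A patient who makes the same corrections in the lead-in scores 7 − 7 = 0, against 0.083 − 0 = 0.083 for the lasting increase. The protocol also does not say that routine corrections count as adjustments.

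Finally, the pooling of better and worse control is inferred. The form's scale and Appendix 1 are not shown, and tabulation may be settled in an analysis plan. This weakens the point for control. It does not remove it for the adjustment count: no section gives that count a direction, and an analysis plan cannot recover a direction that the form did not collect. A single global rating at the end of treatment is no defect.

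**Conclusion.** The point holds as a defect in how two of the four listed secondary endpoints are defined. Followed as written, the adjustment count cannot tell intensified from reduced treatment, and the control endpoint states no direction, in a safety study that leaves the direction of effect open. Free adjustment can blunt HbA1c and home glucose. It need not do so, and extreme values would still appear elsewhere.

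The size cannot be fixed from the documents. On the assumed rates, the power lost by pooling control runs from about 2 percentage points (69% against 71%) to about 69 (2% against 71%), depending on how many placebo patients improve. The correction is worth making because it costs little and makes the two endpoints interpretable.

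**What to change.** Reword the two endpoints in section 4.1.1:

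- Count upward and downward adjustments separately, each as a change from the lead-in.
- Classify each subject's antidiabetic regimen at Week 12 against the lead-in as intensified, unchanged or reduced.
- Report diabetes control as worse, unchanged or better.

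Show the share intensified and the share worse by arm beside HbA1c, each dose against placebo with a confidence interval. Report net change in total daily insulin dose descriptively and in insulin users only. If they are the smaller stratum, section 4.1.6 plans about 12 randomized, or 12 / 3 = 4 per arm, and aims for at least 3 completers per arm.

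The cost is endpoint wording, a few derived variables, and a check that the diary or case report form holds the direction of each adjustment, ideally the dose before and after. The Visit 7 assessment is already planned. Estimates will be imprecise: for 60% against 10% at 13 per arm, the approximate 95% half-width is 1.96 × √(0.6 × 0.4/13 + 0.1 × 0.9/13) = 0.31, or 31 percentage points. No dosing rule is affected.
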